#### Follow-up assessments

Follow-up assessments for both patients and carers will take place at 6 and 12 months post-randomisation. As mentioned previously, an additional 24-month follow-up study is planned but does not form part of the main trial evaluation. Patients will be contacted 2 weeks prior to the due date for these follow-up assessments to arrange an appointment (either by telephone, Microsoft Teams, or face-to-face) to complete the EDE interview and the interview-led section of the AD-SUS at 6 and 12 months post-randomisation. If participants and carers (if participating) have requested paper copies of the questionnaires, they will be mailed out at this point with a free postage stamp for return. If online completion of the questionnaires has been requested, the unique Qualtrics link to access the questionnaires will be emailed to the participant/carer 1 week prior to the due date. The researchers will monitor questionnaire completion. To ensure adherence to study assessment, if participants have not completed the questionnaires nor responded to our interview invitation by the assessment due date, participants will be contacted via telephone and, if required, will be sent further email reminders at 1 and 2 weeks post-due date. Participants will be reimbursed £10 for each completed follow-up assessment (6- and 12-month assessments only).

#### Process evaluation

A qualitative process evaluation will be conducted to investigate views on treatment and how it produced change from the perspective of patients, families and clinicians. Firstly, patients and carers will be approached following completion of the 6-month follow-up and invited to take part in a semi-structured interview. This will investigate positive and negative experiences of treatment, including its perceived short- and long-term effects. Participants will be recruited purposively across study sites to explore a range of opinions (e.g. according to gender, age, baseline ED symptoms, treatment motivation, expectations and experience). Secondly, semi-structured interviews will be conducted with inpatient, day patient and outpatient clinical staff over the course of the trial to investigate their experiences of managing patients, using the decision tool within the context of the two treatment arms, staff training, and their views on providing treatment to this patient group. Thirdly, study discussions about implementation, barriers and facilitators of the treatment approaches and learning events will be audio-recorded to provide further data on the perceived contextual factors at the patient, provider or system level that may contribute to variation in outcomes.

### Measures

Details of the study schedule of measurements and time points, including outcome measures to be collected as part of the additional 24-month follow-up study, can be found in Table 1. No biological samples will be collected in this study.

#### Primary outcome

The primary outcome is BMI (kg/m^2^) at 12 months post-randomisation.

#### Secondary outcomes

##### Clinical outcomes

BMI (kg/m^2^) at 6 months post-randomisation.ED symptomology at 6 and 12 months post-randomisation, measured using the Eating Disorder Examination (EDE) interview [58].Comorbid symptomology at 6 and 12 months post-randomisation, measured using the Depression, Anxiety and Stress Scales-Version 21 (DASS-21, [62]) to assess mood, anxiety and stress symptoms and Obsessive Compulsive Inventory-Revised (OCI-R, [63]) to assess symptoms of obsessive compulsive disorder.

##### Psychosocial adjustment

The Clinical Impairment Assessment (CIA, [64]) will assess psychosocial impairment associated with ED symptoms at 6 and 12 months post-randomisation.The Multidimensional Scale of Perceived Social Support (MSPSS, [65]) will assess the individual’s perceived social support at 6 and 12 months post-randomisation.The Work and Social Adjustment Scale (WSAS, [66]) will assess patients’ perceived functional impairments resulting from AN at 6 and 12 months post-randomisation.The UCLA Loneliness Scale (Version 3) [67] will assess patients’ subjective feelings of loneliness and social isolation at 6 and 12 months post-randomisation .

##### Motivation for change

Motivational rulers (willingness and readiness to change) [53] will assess the importance of personal changes patients’ desire and evaluate their confidence about making those changes at 6 and 12 months post-randomisation.

##### Health-related quality of life

The five-level version of the EuroQol measure of health-related quality of life (EQ-5D-5L, [70]), collected at 6 and 12 months post-randomisation, will be used to assess cost-effectiveness.

#### Additional measures

##### Baseline sample description

All measures designated primary or secondary outcomes at a post-randomisation time point will also be measured at baseline.A purposely designed case record form will assess demographic characteristics of the participants, including gender, ethnicity, employment status, highest level of education, marital status, current living situation, current accommodation status and number of children/dependents, at baseline only.A purposely designed assessor checklist will record date of birth and assess clinical characteristics pertaining to the patient’s ED history, including age at ED onset, previous treatments received, and current treatment. This will be completed by the assessing clinician at baseline only.The Autism Spectrum Quotient (AQ-10, [61]) will assess autism spectrum traits at baseline only.

##### Remission and relapse rates

BMI (kg/m^2^) on a monthly basis from baseline to 12 months post-randomisation.ED symptomology will be measured using the Eating Disorder Examination Questionnaire – short form (EDE-QS, [60]) on a monthly basis from baseline to 12 months post-randomisation.

##### Treatment expectations, acceptability, adherence and completion

A visual analogue scale (VAS, [53]) will assess expectations of treatment effectiveness for both treatment approaches at baseline only.A visual analogue scale (VAS, [53]) will assess experienced treatment acceptability of their allocated treatment at 6 and 12 months post-randomisation, adjusting for expected treatment acceptability at baseline.Intended treatment plan will estimate patient’s treatment need at baseline only.Admission and discharge dates to ED inpatient and day patient services.Number of inpatient days or number of day treatment days (including proportion of remote versus in person days) attended per week.

##### Economic measures

Adult Service Use Schedule (AD-SUS), designed for mental health populations [71, 72] and modified for AN, at baseline, 6 and 12 months post-randomisation. This will include an assessment of all hospital and community health and social care services plus prescribed medications.Hospital Episode Statistics (HES) data from NHS Digital (for participants from England) or Information Services Division (ISD; for participants from Scotland). Data requested will include the number of admission days to Accident & Emergency, specialist ED units and general psychiatric inpatient wards in the year prior to participation in the study, and for 2 years post-randomisation.

##### Covid-19-related variables

A Covid-19 diagnosis and symptom checklist will assess whether participants have been diagnosed with or had suspected Covid-19 and the symptoms they experienced [74], and whether they have received a Covid-19 vaccination at baseline, 6 and 12 months post-randomisation.

##### Carer burden

A purposely designed record form will assess demographic characteristics of the carers (if participating) including age, gender, ethnicity, employment status, the nature of their relationship to the study participant and whether they live with the participant at baseline only.Depression, Anxiety and Stress Scales-Version 21 (DASS-21, [62]) will assess mood, anxiety and stress symptoms at baseline, 6 and 12 months post-randomisation.Eating Disorders Symptom Impact Scale (EDSIS, [73]) will assess the carer’s perceptions of ED-specific burden at baseline, 6 and 12 months post-randomisation.

##### Collected as part of the trial for future secondary analyses (i.e. not presented in or analysed as part of the primary publication)

Treatment experience includes the following:The Perceived Coercion Scale (PCS, [68]) will assess the influence, freedom, control and choice regarding the admission process at baseline and 6 months post-randomisation.The Therapeutic Environment Scale (TESS, [69]) will assess the occurrence of various interpersonal processes in a therapeutic environment at 3 months post-randomisation (included as part of the third symptom monitoring questionnaire).

### Data management

The trial researchers will create a Data Management Plan to document how data will be collected, handled, stored and checked. This will be made available to the trial analysts. Data collected (from paper case report forms and downloaded source data records from Qualtrics) will be entered onto electronic case report forms within the Elsevier InferMed MACRO Version 4 data capture system hosted by Kings Clinical Trials Unit. Two linked online data entry systems will be created to maintain blinding; the first will be used by all approved researchers to enter outcome and additional measure data, and the second will be used by the allocated unblinded researcher to enter trial outcome data with the potential to cause unblinding (including the intended treatment plan, treatment attendance, the Covid-19 checklist, the AD-SUS and adverse events).

Identifying information from participant data will be removed, stored separately and replaced with a unique numeric code, which will be used to identify their data. The master list of names which correspond to participants’ numeric identification codes will be stored electronically and will be password-protected. This information will only be accessible to key researchers involved in the study. All personal and pseudo-anonymised data will either be stored in securely locked filing cabinets at the Section of Eating Disorders, Institute of Psychiatry, Psychology & Neuroscience, King’s College London, or on university servers (on university desktop and laptop computers) and university-approved online storage systems/databases, all of which are password-protected and encrypted. All investigators will have access to the final trial data set without any limits.

### Data monitoring

A Data Monitoring and Ethics Committee has been established due to the risk associated with severe AN. This committee is independent of the study organisers. The Data Monitoring and Ethics Committee will meet on a yearly basis throughout the trial and undertake interim review of the trial’s progress, in the strictest confidence, by reviewing and monitoring trial data, including recruitment figures, data quality, protocol compliance and treatment harm (i.e. adverse events). They will directly report any recommendations or feedback to the Trial Steering Committee who provide overall supervision on behalf of the Project Sponsor and Project Funder and ensure the study is conducted to the rigorous standards set out in the Department of Health’s Research Governance Framework for Health and Social Care and the Guidelines for Good Clinical Practice. The Chair of the Data Monitoring and Ethics Committee is [name] and the members are [name] and [name] [name]. Terms of Reference for the Data Monitoring and Ethics Committee are available on request from the study research team.

#### Premature termination of the trial

No interim analyses will be performed to inform premature termination of the trial. The trial may be prematurely discontinued by the Sponsor or Principal Investigator on the basis of new safety information or for other reasons given by the Data Monitoring and Ethics Committee/Trial Steering Committee, regulatory authority or ethics committee concerned. The trial may also be prematurely discontinued due to lack of recruitment within the internal pilot study. Specifically, we have a stopping guideline in place for if <50% of the desired internal pilot sample size (*n* = 62) is recruited. If the study is prematurely discontinued, active participants will be informed, and no further participant data will be collected.

#### Harms

Adverse events will be spontaneously reported by site investigators to the trial’s research team. Data on adverse events will be collected throughout the trial, and all adverse events will be recorded in electronic case report forms within the trial’s online data entry system. Specifically, we will record the following information: type of adverse event (e.g. physical – weight loss); full details and case description; approximate date of initial occurrence; relationship to the general study procedures or study care pathway (e.g. related or unrelated); whether the event would be considered expected or unexpected; and whether the event is classed as serious. If deemed serious, the adverse event will be escalated to the Principal Investigator who will determine if the event was related to the study and unexpected. If this is the case, the adverse event will be reported to the Sponsor. No follow-up care for adverse events will be given as the intervention does not involve the use of drugs. All adverse events will be reported to the relevant monitoring committees and will be presented as part of the final trial analysis. There is no obvious risk for participants, and we do not expect any adverse events.

### Data analysis

A detailed statistical analysis plan will be developed by the trial statisticians whilst maintaining full blind and agreed with the research team and Data Monitoring and Ethics Committee before the end of the internal pilot. Briefly, all formal comparisons of the two care pathways will follow the intention-to-treat principle. For continuous clinical outcomes variables, such as BMI, linear mixed models will be fitted to the outcome measures at 6 and 12 months to estimate the trial arm differences. The fixed part of these models will contain the explanatory variables of interest (trial arm, time and an interaction term) and also baseline values of outcome variables and randomisation stratifiers, as these variables are known to explain variability in outcome. To account for correlation between the repeated measures at 6 and 12 months, a subject-varying random intercept will be included. For non-continuous outcomes, relevant generalised linear mixed models will be fitted. Results are valid under a missing at random (MAR) missing data generating mechanism that allows earlier outcome values to predict missingness of later ones. In the presence of missing data, should we find that the assumptions underlying the mixed modelling approach are not realistic, then an alternative, more flexible approach such as multiple imputation will be used instead.

To judge non-inferiority of the stepped care approach in terms of the primary outcome (BMI at 12 months), a two-sided 95% confidence interval of the trial arm difference in this clinical measure will be generated and this interval compared with the non-inferiority threshold (0.75 kg/m^2^ decrease in BMI). The threshold defines a region for the trial arm difference in BMI in which the stepped care day patient approach would be considered non-inferior to IP-TAU. To confirm the non-inferiority hypothesis, the whole 95% confidence interval would need to lie within this region. Supplementary subgroup analyses will estimate care pathway differences in treatment-completer populations (defined using the minimal and full treatment completion criteria described previously) to investigate the impact of any treatment non-completion on the non-inferiority assessment. In this context, methods from the causal inference field, e.g. inverse probability weighting, will be used to adjust for variables driving both treatment completion and primary BMI outcome [75]. No other subgroup analyses are planned.

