#### Sample size

The sample size calculation is based on a one-sided non-inferiority test at 97.5% confidence. Previous studies suggested a standard deviation for within-group BMI at 12 months of 2.3 kg/m^2^ [19, 38]. Based on Herpertz-Dahlmann et al. [19], we defined our non-inferiority threshold as a 0.75 kg/m^2^ decrease in BMI for stepped care relative to IP-TAU. If there is truly no difference between stepped care and IP-TAU, then 198 participants per trial arm are needed to be 90% sure that the lower limit of a one-sided 97.5% confidence interval (or equivalent a 95% two-sided confidence interval) for the difference will be above the non-inferiority limit of −0.75. To account for the precision gain due to including baseline BMI in the modelling, we applied a deflation factor (0.78, based on a pre-post correlation of 0.47, [38]) to the estimated sample size [52]. We also inflated the requirement to account for 20% dropout at 12 months based on our previous studies [53, 54]. This gave a final sample size requirement of 193 per trial arm (*n* = 386 in total).

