The clinical team will complete an initial decision tool (described below) on all participants when assessing the patient’s eligibility for the study (i.e. prior to randomisation) to help decide on whether the patient ought to start this treatment pathway with inpatient or day patient treatment. Within the stepped care treatment arm, further weekly decision tools will be completed for the duration of intensive treatment (i.e. in- or day patient treatment) with clear rules around patients’ suitability for stepping down into specialist day patient treatment (or stepping up from day patient treatment into inpatient treatment if necessary, in the case of deterioration or relapse). Patients should step down to day patient treatment within 1 month of being at an appropriate level of risk, as detailed below. Day patient treatment will involve a full-time programme covering 4–5 days a week with 2–3 meals per day, multidisciplinary support (including psychiatrists, psychologists, dieticians, nurses and others) and high-quality evidence-based psychological interventions for patients and their carers. There is no concomitant care prohibited during the trial. Patients will return home for weekends and evenings. As a result of the Covid-19 pandemic, a protocol change was made so that day patient treatment can now also be delivered using a blended or hybrid approach, combining both remote (video-conferencing) and physical attendance at day service activities (e.g. supported meals, groups) and psychological therapies. Having this flexibility will allow us to react to the constantly changing situation and continue with the trial if later Covid-19-related local/national lockdowns are enforced resulting in services having to temporarily halt face-to-face treatment. Data will be collected from the clinical teams until end of follow-up (i.e. 12-months post-randomisation) to allow us to fully characterise patients’ treatment. This includes admission and discharge dates for day patient treatment and any inpatient admissions (if required for medical stabilisation), weekly day patient treatment attendance, and also proportion of remote versus physical attendance.

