#### Screening

Any patients deemed by their assessing or treating ED clinician to be in need of intensive treatment (in- or day patient treatment) will be invited to participate in the study. They will be approached by their assessing/treating clinician, informed that the study is taking place, and given a brief description of it. Whilst it is anticipated that most patients will be recruited from community/outpatient settings, some patients may be recruited from inpatient units, e.g. if they were originally admitted as an emergency and did not have capacity to consent to study participation prior to admission. For those interested, the clinician will complete a brief assessor checklist to screen for eligibility and assess the patient’s capacity. If eligible, the clinician will complete the decision tool (described above) and an intended treatment plan to assess whether the treatments pathways are being offered as planned. Clinicians will then ask the patient for consent to be contacted by the research team. The research team will provide further information, answer any questions and obtain written informed consent for randomisation and data collection from the patient. There is also an optional carer component designed to assess carer burden, and so, at this point patients will be asked for consent to involve their main carer within the research. If consent is given, the carer will be invited to participate, and informed consent for data collection will be obtained. Informed consent from both the patient and carer (if participating) will be obtained by a member of the research team before randomisation, either online (via Qualtrics), by post, or in person.

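### The primary model omits two available baseline measures, the decision-tool result and inpatient status at randomisation, and the closed subgroup list leaves no randomised comparison by expected starting setting

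*Protocol article*

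**What the plan says.** **Covariates.** Under Data analysis, the fixed part of the mixed model holds trial arm, time, their interaction and "also baseline values of outcome variables and randomisation stratifiers, as these variables are known to explain variability in outcome". The Randomisation section names the stratifiers: previous inpatient treatment, illness duration (up to or over 3 years) and recruitment centre.

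**Subgroups.** The same section plans supplementary analyses in treatment completers, weighted for variables that drive completion and outcome. It does not name those variables. It then states "No other subgroup analyses are planned".

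**Decision tool.** Under Stepped care day patient approach: "The clinical team will complete an initial decision tool (described below) on all participants". This is done before randomisation and helps decide in which setting stepped care would start. The Decision tool section says that patients with any red indicator, or several amber ones, will usually be inpatients under stepped care. Those mainly green start in, or step down to, day treatment.

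**Inpatient status.** Under Screening: "some patients may be recruited from inpatient units, e.g. if they were originally admitted as an emergency". Definition of treatment completion confirms that some participants are inpatients when randomised. Current treatment is on the baseline assessor checklist (Additional measures, Baseline sample description).

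**The concern.** Both measures exist before randomisation, in both arms, and bear on how far care can differ between arms. Neither is a stratifier, a listed covariate or a subgroup. Previous inpatient treatment is history and does not stand in for being an inpatient at randomisation.

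Two things are at stake.

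1. **Precision.** A baseline risk measure that predicts 12-month BMI beyond baseline BMI would narrow the primary confidence interval.
2. **Interpretation.** Patients whose tool result points to an inpatient start receive inpatient care early on in either arm. The more of them there are, the less an overall non-inferiority result says about starting in day treatment, which services will want to know.

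The only planned analysis that comes near the second question is the completer analysis. Completion in the stepped care arm requires 8 weeks or more on the full-time day programme, whereas in the inpatient arm it counts inpatient weeks after randomisation. Stepped care completers are thus selected on having reached and stayed in day care, and inpatient-arm completers are not. Weighting may reduce the resulting imbalance, but the contrast no longer rests on randomisation alone.

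**Working it through.** **Inputs (Sample size section).** The test: "The sample size calculation is based on a one-sided non-inferiority test at 97.5% confidence". The spread: "a standard deviation for within-group BMI at 12 months of 2.3 kg/m^2". The margin: BMI under stepped care lower by 0.75 kg/m2. The unadjusted size: "If there is truly no difference between stepped care and IP-TAU, then 198 participants per trial arm are needed to be 90% sure". Also a pre-post correlation of 0.47 (deflation factor 0.78), 20% dropout, and 193 per arm (386 in total).

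**Step 1: reproduce the plan's figures.**
- n per arm = 2 × (2.3 × (1.960 + 1.282) / 0.75)² = 197.6, rounded up to 198. This agrees.
- Deflation = 1 − 0.47² = 0.779. Then 198 × 0.78 / 0.80 = 193.05, or 192.8 with the unrounded factor. This agrees with 193.
- Evaluable per arm = 193 × 0.80 = 154.4. Residual SD = 2.3 × √0.7791 = 2.03. SE = 2.03 × √(2/154.4) = 0.231. The 95% CI half-width is 1.96 × 0.231 = 0.453 kg/m2.
- Power at a true difference of zero = Φ(0.75/0.231 − 1.96) = 90.1%.

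The planned power is therefore reached with baseline BMI alone and does not depend on the two omitted measures.

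**Step 2: what the two covariates could add.** The article gives no figure for the extra share R of residual variance explained, so R is assumed. SE becomes 0.231 × √(1 − R).

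| R (assumed) | SE | CI half-width (kg/m2) | Power | Total N for 90% |
|---|---|---|---|---|
| 0% | 0.231 | 0.453 | 90.1% | 386 |
| 2% | 0.229 | 0.448 | 90.6% | 378 |
| 5% | 0.225 | 0.441 | 91.5% | 368 |
| 10% | 0.219 | 0.430 | 92.8% | 348 |

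BMI is itself one of the tool's indicators and is already in the model, so the lower rows should not be taken for granted.

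**Step 3: what a baseline subgroup could show.** For a subgroup holding a share s of patients (assumed; the article gives none), SE = 0.231 / √s.

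| s (assumed) | CI half-width (kg/m2) | Power against the 0.75 margin |
|---|---|---|
| 30% | 0.83 | 43% |
| 50% | 0.64 | 63% |
| 70% | 0.54 | 77.5% |

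At 30% the half-width exceeds the margin, so even an observed difference of zero would not show non-inferiority. The SE of the difference between two strata is 0.46 at a 50:50 split and 0.50 at 30:70. The estimate can describe but not confirm.

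**The case against.** The strongest reply is that the trial tests a pathway. Study objectives and Stepped care day patient approach define the intervention as day treatment with optional initial inpatient stabilisation, so shared inpatient care is part of what is compared. Study design records that a trial restricted to patients able to start directly in day treatment was considered and rejected, because it would exclude many patients and limit generalisability. Omitting a baseline covariate does not bias a randomised comparison, and limiting underpowered subgroups is a defensible choice. All of this stands.

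A reader might infer something stronger: that shared care dilutes the contrast and so inflates the chance of a false claim. Suppose that patients starting as inpatients show no difference, and that the rest have a true deficit of 0.75. With 30%, 50% or 70% starting as inpatients, the overall difference is −0.53, −0.38 or −0.23, and non-inferiority is declared with probability 16%, 37% or 62%. The documents do not support reading these as error rates. Each overall difference lies inside the −0.75 margin, so declaring non-inferiority is correct for the pathway question; at a true overall −0.75 the error stays at 2.5%. The shares are assumed. Zero contrast over 12 months also conflicts with the article, under which stepped care patients are to move to day treatment early while the inpatient arm is to be kept in until its course is complete.

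Nor do the documents say that the tool determines prognosis, or that the question goes wholly unexamined. The completer definition removes stepped care patients who stayed almost entirely inpatient, the unnamed weighting variables may include both measures, and setting and attendance are recorded. What survives is narrower: no planned comparison by expected starting setting keeps the protection of randomisation.

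**Conclusion.** The point holds as an improvement the plan forgoes. The primary comparison is valid and reaches its stated power. Adding the two measures might raise power from 90.1% to about 90.6-92.8%, on an assumed 2-10% of further residual variance explained; the true gain is unknown and may be smaller.

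The greater benefit lies in interpretation. Since the article's own reason for rejecting a day-only design implies that many eligible patients could not start in day treatment, an overall non-inferiority result should not be read as showing that a day-patient start is itself non-inferior. A completer analysis selected on treatment received cannot settle that. A comparison within baseline tool categories would respect randomisation, though with an interval too wide to confirm anything.

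The subgroup list is expressly closed in the article, so that part is not simply detail left to the statistical analysis plan. The choice of weighting variables may well be settled there.

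**What to change.** 1. **Primary model.** Pre-specify as additional fixed effects the baseline decision-tool category and inpatient status at randomisation (yes/no).
2. **Classification.** State in advance how the tool's traffic-light result maps to an expected inpatient or day-patient start. The article describes no recorded binary result, and its rules use qualifying terms. The mapping is for analysis only and leaves clinical use of the tool unchanged.
3. **Completer analysis.** Name both measures among the variables used for the completion weights.
4. **Subgroups.** Amend the sentence "No other subgroup analyses are planned" to allow one supportive estimate of the 12-month arm difference, with its 95% CI, by baseline decision-tool category. Label it descriptive, with no non-inferiority claim attached.

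The cost is wording in the analysis plan, a few extra model parameters, and a subgroup interval with a half-width of about 0.54-0.83 kg/m2. Sample size, randomisation and treatment are unaffected. Two practical checks are needed. The baseline tool result must be held in the trial data for both arms, since the article says that it is completed but not where it is stored. And because the trial statistician is blind only until the analysis plan is signed off, any later change should be decided by those still blind to allocation.
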